### Sample size and power calculation

4.1

The target sample size of participants was estimated based on the previous studies among health care workers or general population under the COVID-19 outbreak: prevalence of mental health problems (depression, anxiety, stress, and psychological distress) with a range of 5.2% to 71.5%^[16–25]^ and 3.3% to 75.5%^[20,22,23,26–31]^ for health care workers and the general population, respectively. To compensate for a design effect of 2.0 and a completed responses rate of 60%, a target of at least 1182 health care workers and 1310 general populations is required to complete the online survey for each wave of the survey to ensure a power of 80% and a 0.05 type I error. However, there will be no restriction on the number of participants in this online survey.

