### Statistical analysis

4.3

Data synthesis will be conducted separately for health care workers and the general population. Descriptive data statistic will be summarized as number (percentage) or mean ± standard deviation, or median with an interquartile range as suitable. Differences in responses with respect to baseline characteristics will be assessed using Fisher exact test and unpaired *t* test or Wilcoxon rank-sum test for categorical and continuous data, respectively.

For all estimates of prevalence, we will weight data for all wave surveys (wave I, II, III, and IV) analyses under the complex design of the survey—weighting adjusted for noncompleted responses survey and national rates of unemployment at the time of each survey. Population control totals for age by sex and region, and the rate of internet use will be obtained from the National Statistic Office, Ministry of Information and Communication Technology, Thailand. The estimates of the prevalence of mental health status will be calculated and reported along with the 95% confidence intervals (CIs). Subgroup analyses stratified by key characteristics (eg, age, sex, region, working position [frontline or nonfrontline], hospital type, and region of residence) will also be done to analyze the proportion differences.

Moreover, an online wave II, III, and a 1-year follow-up survey will be compared to assess the long-term responses and resilience capability on the prevalence of mental health status among health care workers and the general population. Nonoverlapping 95% CIs are indicating statistical differences in the prevalence between the survey wave or subgroups, with the *P* values that are based on the trend tests. The absolute change in prevalence will be calculated with the formula: Δ = (1/duration between survey) × (p_last_ – p_initial_), with variance estimated as (var [p_last_] + var [p_initial_])/(duration between survey), where p_last_ and p_initial_, stand for the last prevalence and initial prevalence, respectively. Trend analysis will be performed to identify the effect of overtime across the study time frame.

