For the survey—wave I, the crude association between participant characteristics will be assessed through the univariable logistic regression models to identify the candidate risk factors of early mental health problems. Subsequently, risk factors with a *P* value <.100 were then included in the multivariate logistic regression analysis with the stepwise backward method. The final model was also determined for multicollinearity by investigation of the variance inflation factors of the risk factors within the multivariable model. The effect estimates of the final risk factors model for mental health problems will be expressed as odds ratios (ORs) with corresponding 95% CIs.

For the repeated cross-sectional survey, we will combine the data from the wave I to wave IV survey to analyze changes in the mental health status. We will perform multilevel logistic regression models with random intercepts to explore associations with individual-level and region-level/hospital-level predictors. The survey wave will be analyzed as a level 1 variable with a fixed effect to distinguish between study survey waves across the study time frame.

To improve the generalizability of study findings, we also plan to perform an ancillary systematic review and meta-analysis by incorporating data from our findings to all available evidence regarding the mental health and psychosocial problems among health care workers and the general population. The prespecified protocol for systematic review has been registered in the International Prospective Register of Systematic Reviews (PROSPERO: registration number, CRD42020177120). Globally, the mental health problems attributable to the general population during the COVID-19 pandemic will be estimated by multiply the pooled prevalence of our findings against the United Nations’, world population report.

Missing data or noncompleted responses will be excluded from the primary analyses. However, a multiple imputation method will be performed in the sensitivity analysis. All analyses will be performed using Stata software version 14.0 (StataCorp, LP) and Microsoft Excel version 2016. They will be 2-tailed and *P* value <0.05 will be considered statistically significant.

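### Wave I risk factors are chosen by P<.100 screening and backward stepwise, then reported with ordinary ORs and CIs; the model as written also lacks the random intercepts used in the combined-wave model

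*Protocol article*

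**What the plan says.** Section 4.3 of the protocol article gives the wave I model in three steps. Participant characteristics "will be assessed through the univariable logistic regression models to identify the candidate risk factors of early mental health problems". Factors with a univariable P "value <.100 were then included in the multivariate logistic regression analysis with the stepwise backward method". After a check of variance inflation factors, "The effect estimates of the final risk factors model for mental health problems will be expressed as odds ratios (ORs) with corresponding 95% CIs". The P value for removal in the backward step is not given. This is the only wave I analysis described for the early predictors named in the third objective (section 2).

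Three other statements bear on it:

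- Section 4.1 sizes the survey with an allowance for dependence or unequal weighting: "To compensate for a design effect of 2.0 and a completed responses rate of 60" per cent.
- Section 4.3 attaches weighting and the complex survey design to the prevalence estimates of all four waves.
- Section 4.3 gives the combined wave I to IV analysis a multilevel logistic model with random intercepts and region- or hospital-level predictors.

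The wave I paragraph mentions neither weights, nor robust variance, nor random intercepts.

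**The concern.** The selection rule uses the same data twice: once to decide which factors stay, and again to estimate them as if the model had been fixed in advance. A weak factor stays only when its estimate happens to be large, so the published OR is too far from 1 and its CI too often misses the truth. The univariable screen has a separate fault. A variable whose effect is masked by another looks null alone, never enters the multivariable model, and leaves the other ORs unadjusted for it.

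The second issue is consistency. Recruitment through hospital staff networks and by snowballing (sections 3.2 and 3.3) makes correlated answers plausible, and the combined model allows for them. If the wave I model does not, its CIs may be too narrow. Its ORs would also be population-averaged while those of the combined model are conditional on hospital or region, so early and later predictors could not be compared like for like. The procedure is repeated over several outcomes and two populations.

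**Working it through.** **Inputs from the documents.** Targets of 1182 health care workers and 1310 general population per wave, design effect 2.0, completion 60%, power 80%, two-sided 0.05, and planning prevalences from 5.2% to 71.5% and 3.3% to 75.5% (sections 4.1 and 4.3). Section 3.4 lists 21 participant characteristics, with further hospital items for health care workers.

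**The plan's own figure.** Removing the stated inflation gives base sizes of 1182 × 0.6 / 2 = 354.6 and 1310 × 0.6 / 2 = 393. The article gives only prevalence ranges and no margin or effect size, so the targets cannot be reproduced from it. Nothing below depends on them beyond the use of n = 1182 and, for the event counts, 1310.

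**Selection alone, independent responses.** Assumed: n = 1182, prevalence 30%, 25 balanced binary candidates of which one has a true effect, screen at P<0.10, backward removal at P<0.05.

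- Simulation of 600 runs with a true OR of 1.25: retained in 42.3% of runs, mean OR when retained 1.41, coverage 92.1%. That coverage rests on about 254 retained runs, so its Monte Carlo standard error is √(0.921 × 0.079 / 254) = 1.7 points. A repeat with 6000 runs gave 1.41 and 93%.
- Closed-form check: SE of the log OR = √(4 / (1182 × 0.3 × 0.7)) = 0.127, and ln 1.25 / 0.127 = 1.758.
  - Probability of retention ≈ 1 − Φ(1.960 − 1.758) = 0.420.
  - Mean retained z = 1.758 + φ(0.202) / 0.420 = 2.689, so the mean OR is exp(2.689 × 0.127) = 1.41.
  - Coverage given retention = (0.975 − 0.580) / 0.420 = 0.94.
- The same formulas, with both tails, for a true OR of 1.10 (z = 0.751): retention 0.117, mean OR when retained 1.34, coverage 0.0883 / 0.1167 = 0.76. For a true OR of 1.50 (z = 3.194): mean OR when retained 1.54, coverage 0.97. The distortion therefore belongs to weak effects.
- Null factors in the 600 runs: 1.2 of 24 retained, at least one in 71% of runs. Plain testing at 0.05 with no selection gives 24 × 0.05 = 1.2 and 1 − 0.95^24 = 71%.

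**Events.** At the low end of the planning ranges, 0.052 × 1182 = 61 and 0.033 × 1310 = 43 events. Against 21 candidates that is 61 / 21 = 2.9 and 43 / 21 = 2.1 events per candidate, where stepwise choice is least stable.

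**Clustering.** If a design effect D applied to a coefficient and were ignored, the SE would be too small by √D, the true coverage of a nominal 95% CI would be 2Φ(1.96/√D) − 1, and a null factor would pass the screen with probability 2(1 − Φ(1.645/√D)).

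| D for the coefficient (assumed) | SE factor | True coverage | Null factor passes P<0.10 |
|---|---|---|---|
| 1.0 | 1.00 | 95.0% | 10.0% |
| 1.25 | 1.12 | 92.0% | 14.1% |
| 1.5 | 1.22 | 89.0% | 17.9% |
| 2.0 | 1.41 | 83.4% | 24.5% |

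The last row, with type I error 1 − 0.834 = 16.6%, applies the plan's design effect in full to every coefficient. The documents do not say which row applies to which factor.

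**The case against.** The best defence is that the article condenses a fuller plan. It never says that weights or clustering are left out of wave I, and its reference to analyses of all waves under the complex design leaves some room, although that sentence is tied to prevalence. This stands: the text supports saying that no cluster-aware variance is specified, not that clustering is ignored. It does not help the selection rule, which is stated outright.

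A reader might go further and infer four things that the documents do not support:

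- That the design effect of 2.0 measures weighting and clustering that the wave I model throws away. Section 4.1 gives no source for it.
- That coverage is therefore 83% and type I error 16.6%. A design effect for a prevalence does not carry over in full to regression coefficients. Any part due to unequal weights inflates the variance of a weighted estimator, not of an unweighted one. Any part due to correlation acts mostly on hospital- or region-level factors.
- That leaving out weights biases the ORs. It need not, if the model is correctly specified and includes the weighting variables; age, sex and region are among the candidates. Nor can weights cure the selection in a convenience and snowball sample.
- That screening plus stepwise floods the model with false factors. With independent data the count equals the nominal 0.05 rate, and a full model tested at 0.05 would give the same number.

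**Conclusion.** The concern holds for the selection rule. Followed as written, it exaggerates weak retained ORs and makes their CIs under-cover, and it can drop confounders that are null univariably. For a true OR of 1.25 the average retained estimate is about 1.41 and coverage 92 to 94%; it is worse for weaker effects and fades for strong ones. These figures rest on the assumed sample, prevalence, balanced independent candidates and 0.05 removal level.

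It holds in a limited way for clustering. The wave I model as written does not match the combined-wave model or the sample-size assumption. If responses are correlated within hospitals or regions, its CIs are too narrow, chiefly for factors measured at those levels. The size cannot be derived from the documents, and 83% coverage is an upper illustration, not an estimate. This is a cheap improvement worth making. It does not affect the prevalence estimates.

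**What to change.** - Replace screening and stepwise selection with one pre-specified covariate set per outcome, drawn from the characteristics in section 3.4, and report the full model. Use penalised likelihood where events are few.
- Fit it with the same region or hospital random intercepts as the combined wave I to IV model, so that early and later ORs have the same meaning.
- If stepwise selection is kept, state its removal threshold and report it only as exploratory, beside the full model.
- Add a survey-weighted fit as a sensitivity analysis, and say explicitly that the main wave I model is unweighted if that is the intention.

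No new data are needed beyond what the combined model already requires. The cost is some extra model fitting, wider CIs and a longer model table.

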## Ethics and dissemination

5

### Ethics approval and consent to participate

5.1

Ethics approval has been granted for the study by the Committee of Research Ethics in Faculty of Public Health (ET010/2020) and Faculty of Pharmacy (23/2563), Chiang Mai University. This study protocol will be performed according to the Declaration of Helsinki. All protocol amendments will be submitted to the ethics committees for approval. The protocol version 2–2020, dated April 23, 2020 was used to prepare this manuscript.

All respondents are required to fill a written informed consent (embedded on the first page of the survey questionnaire) before participating in this survey. If the participant answers “Yes” to the first question of the form, they automatically agree to participate and will be the survey. By using the skip-logic survey method, users who disagree with the informed consent question will be conducted to the end of the survey. No respondent is forced to participate in the survey and their participant is based on their agreement that can be withdrawn at any time. All participants have the right to leave a specific question unanswered or withdraw from the survey any time if they feel uncomfortable answering any question. Moreover, no one even the research team will know individual answers to this questionnaire.

### Autonomy and confidentiality

5.2

All participants have the right to leave a specific question unanswered or withdraw from the survey any time if they feel uncomfortable answering any question. Moreover, no one even the research team will know individual answers to this questionnaire. All data are anonymous and are not able to identify the participants. The collected electronic data will remain confidential and only authorized team members will have access to it. Furthermore, data will be completely encrypted and coded for use mainly in statistical analysis using computer software.

### Dissemination of results

5.3

Our findings will be disseminated through public, scientific, and professional meetings, and publications in peer-reviewed journals. Summary results in the lay written manner will also be available to the public. The investigators commit to reporting the results in line with the Strengthening the Reporting of Observational Studies in Epidemiology (STROBE) Statement: guidelines for reporting observational studies^[32]^ and Improving the quality of Web surveys: the Checklist for Reporting Results of Internet E-Surveys (CHERRIES).^[33]^

## Discussion

6

Since the end of December 2019, the Chinese city of Wuhan has reported novel pneumonia caused by coronavirus disease 2019 (COVID-19) pneumonia outbreak (previously referred to as “Wuhan pneumonia” or 2019 Novel Coronavirus [2019-nCoV]).^[34]^ Due to potentially serious health outcomes, from January 23, 2020, Wuhan and other regions in mainland China have adopted strict quarantine measures to control the widespread of the COVID-19 outbreak.^[34]^ Subsequently, person-to-person transmission has been recorded outside mainland China, which is spreading domestically and internationally. On January 30, 2020, the World Health Organization (WHO) declared the global COVID-19 outbreak a public health emergency concern, consequently characterizes as a pandemic on March 11, 2020. As of April 26, 2020—situation report-97—a total of 2,810,325 confirmed cases with 193,825 confirmed deaths have been documented globally.^[35]^

The negative emotion and psychosocial distress may occur among frontline health care workers who have directly involved with the COVID-19 patients, which characterized by unintentional missing, trigger events considered into the mistake, and delay treatment owing to the communication failure. A cross-sectional study of 1257 health care workers who treated patients exposed to COVID-19 in multiple regions of china (including Wuhan) by Lai et al, 2020,^[16]^ revealed that participants reported symptoms of depression 50.4%, anxiety 44.6%, insomnia 34.0%, and distress 71.5%. Not surprisingly, frontline health care workers were associated with a higher risk of depression (OR, 1.52; 95% CI, 1.11–2.09; *P* = .010), anxiety (OR, 1.57; 95% CI, 1.22–2.02; *P* < .001), insomnia (OR, 2.97; 95% CI, 1.92–4.60; *P* < .001), and distress (OR, 1.60; 95% CI, 1.25–2.04; *P* < .001).

The affected people were also subject to societal rejection, discrimination, and stigmatization. Evidence suggests that the psychological impact of quarantine is wide-ranging, substantial, and can be long-lasting, including post-traumatic stress symptoms, confusion, and anger.^[36]^ A wide range of psychological and nonpsychological outcomes was reported and has negative consequences for segregated patients among isolation hospitalized patients who are infectious to contain the risk of infection.^[37]^ Moreover, loneliness, anger, frustration, and boredom could be experienced by individuals in the quarantine period. Interestingly, the previous report among the exposed individuals in the quarantine period with the Middle East respiratory syndrome coronavirus (MERS-CoV) outbreak in Korea found that 7.6% and 16.6% expressed anxiety and feelings of anger symptoms, respectively.^[38]^

To our knowledge, this is the first prospective, a repeated cross-sectional study among health care workers and the general population in Thailand. Given the limited evidence at a national level, our study will comprise an early- and long-term mental health status and responses to the COVID-19 outbreak in Thai health care and the general population. Our findings will also plan to perform an ancillary analysis by incorporating all available evidence to further systematic review and meta-analysis. However, as this study leverages online survey data, thereby, responses rates and incomplete information in some questionnaires may limit our findings.

## Conclusion

7

This prospective repeated cross-sectional study, the national-based online survey will report the prevalence of mental health and psychosocial problems among health care workers and the general population in Thailand during the time of the COVID-19 pandemic. Findings from our study can aid health care professionals, public health officials, and public society by quantifying and identify factors that may accelerate or mitigate the negative impact of the COVID-19. This information can inform the design of strategies for public policy and cope with mental health and psychosocial life events. Our findings will disseminate in the forms of public and scientific meetings along with the peer-reviewed publication.
